#### Measures of Secondary Outcomes

The secondary outcomes will be measured as described here. Physiological parameters will be continuously measured using the Nellcor pulse oxygen saturation meter (Covidien), an approved and validated device. The occurrence of side effects will be collected from arrival on site to discharge from the study using a checklist of common side effects experienced while using VR and also related to dental medication. The length of the procedure will be measured and collected for every participant and will be compared with the average duration for a similar procedure that will have been measured prior to the study by the clinic’s personnel. Rescheduling of procedures in the event that cooperation is impossible will be noted. Salivary amylase levels, as a stress biomarker, will be measured before and after the dental procedure as described in the following section.

#### Measurement of Salivary Amylase

Saliva samples will be collected from all children in this study at 2 different study time periods: before (T0) and after (T2) the intervention. Salivary alpha-amylase has been recognized and validated as a reliable and specific marker for autonomic nervous system activity and has been proposed as an alternative biomarker for stress [12]. Alpha-amylase sampling has been performed in previous studies to evaluate DFA for children undergoing dental procedures [28-30]. Alpha-amylase, as a salivary biomarker, can be considered an important and noninvasive tool for assessment of anxiety-related events, such as dental extraction and other treatment, for children [28,31].

Salivary samples will be collected using a sterile dental cotton swab from under the tongue 10 minutes before and 10 minutes after the procedure and stored immediately within a sterile vile in a research-specific on-site freezer. Samples will be collected by the dental resident and taken to the laboratory. Results will be entered in REDCap for analysis after the study.

Table 1 provides an overview of which questionnaires will be answered by which respondents during the study.

**Table 1 table1:** Questionnaires and corresponding respondents.

Questionnaires	Respondents
Parent or legal guardian satisfaction	Parents or legal guardians
Health care professional satisfaction	Health care professional
Anxiety score, physiological parameters	By proxy through research assistants

### Study Proceedings Including Data Collection

Participants will be identified by the resident dentist through the appointment scheduling system as requiring any dental procedure. Since DFA can arise from multiple different procedures such as simple cleaning to teeth extraction, dentists at the clinic will identify possible participants to include based on their cooperation, personality, and fears. An individual independent to the study will review consent with participants and parents. Written consent by the parents or legal guardian—including the child’s assent—will be obtained on arrival at the clinic the day of the procedure while completing the preprocedural questionnaire.

After verifying that the participant meets all the inclusion and exclusion criteria, the dental resident will log into REDCap only 10 minutes before the start of the intervention to minimize the risk of bias toward the intervention and to obtain the group allocation and announce it to the participant. Because of the nature of VR, no blinding of staff, participants, and parents or legal guardians will be possible. Baseline data collection prior to the dental procedure, including the sociodemographic questionnaire, recording of physiological parameters, and salivary alpha-amylase sampling, will take approximately 15 minutes to complete. The VR headset will be adjusted for the child’s size, and approximately 5 minutes will be allotted for children to familiarize themselves with the room, equipment, and game before the start of the procedure.

The intervention will last the entire time of the dental procedure, and the duration will be recorded for every patient. DFA assessment by proxy using the Venham Anxiety and Behavioral Rating Scale will be performed on site by the dental resident present and will also be filmed (if consent was given) to be evaluated by another member of the team at a later date.

As per the clinic’s protocol, if a child becomes restless and cooperation is impossible, the child will be held by his or her parents for the remaining duration of the procedure if it cannot be safely stopped at that time or if the procedure is considered an emergency. If the procedure can be safely stopped, rescheduling will be discussed with the parents including the possible need for sedation. The involvement of parents will be recorded as well as any other distractions used during treatment such as the use of stickers, teddy bears, or music.

All side effects and medication used will be recorded. The former will be transmitted to the ethics committee if needed. As VR has the potential to cause nausea, dizziness, and motion sickness, should participants experience any of these, they will be dealt with according to the clinic’s protocols. If participants experience adverse side effects and the attending dentist and dental assistant have been informed, the treatment will be safely discontinued. All instruments in the mouth will be removed. The VR device will be removed from the participant. The dental chair will be placed in a comfortable position, and the patient will rest until they feel comfortable and recovered. The option of continuing the treatment (without the VR headset) or postponing the treatment to another day will be discussed. Postprocedure salivary alpha-amylase sampling and completion of questionnaires regarding parent and health care professional satisfaction levels after the dental procedure will take approximately 20 minutes. Equipment used by children will be disinfected before the next participant arrives.

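### The allocation is announced at the same 10-minute mark as the T0 saliva sample, and nothing requires T0 to be complete first, so baseline can be measured after the arm is known

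*Protocol article*

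**What the plan says.** All places are in the protocol article.

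- **Allocation** (Study Proceedings Including Data Collection): after the eligibility check, "the dental resident will log into REDCap only 10 minutes before the start of the intervention", and the purpose is "to obtain the group allocation and announce it to the participant".
- **T0 saliva** (Measurement of Salivary Amylase): samples are taken "from under the tongue 10 minutes before and 10 minutes after the procedure". The dental resident collects them.
- **Baseline collection** (Study Proceedings, after the announcement): the sociodemographic questionnaire, "recording of physiological parameters, and salivary alpha-amylase sampling, will take approximately 15 minutes to complete".
- **Familiarisation** (Study Proceedings, after the baseline sentence): the headset is fitted and "approximately 5 minutes will be allotted for children to familiarize themselves with the room, equipment, and game before the start of the procedure".
- **Link between the two clocks** (Study Proceedings): "The intervention will last the entire time of the dental procedure", so the intervention and the procedure start together on the plain reading.
- **Blinding** (Study Proceedings): "no blinding of staff, participants, and parents or legal guardians will be possible".
- **Venham rating**: Study Proceedings gives the on-site rating to the dental resident. Measures of Primary Outcomes and Table 1 give it to research assistants. Either way the on-site rater is unblinded staff. Study Time Points lists a T0 rating without a clock time.
- **Use of T0**: Secondary Outcomes compares physiological parameters with baseline. Amylase is sampled only at T0 and T2. Statistical Analysis names the T0 anxiety score in its description of the T2 comparison.

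**The concern.** A baseline value is a safe reference in a randomised comparison because the arm cannot have influenced it. Here the arm is announced to an anxious child shortly before treatment, and the measures concerned are observed anxiety, pulse and a salivary stress marker. The Introduction itself treats anticipation as part of the main trigger of dental fear. Hearing that one will have the game, or only the wall TV, could shift these measures. It could also shift how an unblinded rater scores the child.

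If T0 is taken after the announcement, it is a post-randomisation value. A change from such a T0, or a T2 comparison that takes it into account, may lose part of the effect or gain a spurious one. No later analysis can recover an uncontaminated baseline.

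**Working it through.** No sample size, power or alpha figure depends on this point, so there is no stated figure to reproduce. The check is a timeline in minutes, with the start of the procedure at 0.

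**Inputs from the protocol**
- T0 swab at −10.
- Baseline collection lasts about 15 minutes.
- Familiarisation lasts about 5 minutes before the procedure.
- Allocation is opened 10 minutes before the intervention starts.

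**Allocation time, a**
- If the intervention starts with the procedure: a = 0 − 10 = −10.
- If it is taken to start with familiarisation at −5: a = −5 − 10 = −15.

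**Placement of baseline, from s to e.** The protocol does not fix this, so three placements are tried:
- −15 to 0, running up to the procedure (this overlaps familiarisation);
- −20 to −5, followed by 5 minutes of familiarisation, which matches the order of the text;
- −25 to −10, ending with the swab.

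**Baseline minutes after disclosure** = max(0, e − max(s, a)).

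| Baseline window | a = −10 | a = −15 |
|---|---|---|
| −15 to 0 | 0 − (−10) = 10 | 0 − (−15) = 15 |
| −20 to −5 | −5 − (−10) = 5 | −5 − (−15) = 10 |
| −25 to −10 | −10 − (−10) = 0 | −10 − (−15) = 5 |

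**Swab relative to disclosure** = −10 − a. This is 0 minutes when a = −10, and 5 minutes after disclosure when a = −15.

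On the plain reading, then, the swab and the announcement share one nominal minute and one person does both. One must come first, and the protocol does not say which. No placement puts the nominal swab time before the nominal disclosure time.

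**What a protected T0 would need.** With log-in kept at −10 and 15 minutes of collection finished first, baseline starts at −10 − 15 = −25 or earlier. The swab then has to be taken before the −10 mark now stated.

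**The case against.** The strongest reply is that the order is inferred, and sentence order is weak evidence here. The baseline sentence includes the sociodemographic questionnaire, which Study Time Points places in the waiting room and which is completed around consent on arrival. Part of baseline therefore precedes log-in, and the sentence may give a duration and not a sequence. Two rounded 10-minute marks are also met by a resident who swabs first and logs in straight afterwards. Multimedia Appendix 1, which holds the study time points, is not shown and may settle the order. Finally, this is a 20-child pilot whose recruitment and completion rates do not use T0, and its allocation concealment is sound.

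Much of this stands. The range must start at 0 of 15 minutes, the questionnaire is hardly exposed, and concealment is not in question. The late log-in is a sensible guard against foreknowledge at enrolment. But the article itself publishes both marks and both durations, and these need reconciling whatever the appendix says. Being a pilot does not remove the point either: preliminary anxiety effects are listed among the primary objectives, effect sizes are to be assessed, and the results are meant to inform a larger trial.

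A reader might also infer more than the protocol supports:
- **That T0 may follow trying the headset.** The text describes fitting after baseline, and a swab at −10 precedes familiarisation at −5.
- **That T0 is the adjustment covariate and the reference for every change score.** Statistical Analysis does not clearly state a T0-adjusted model. Only the physiological parameters are expressly compared with baseline.
- **That baseline balance can no longer be checked.** Age, sex, ethnicity, procedure, medication and special-needs status cannot change on hearing the arm.

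**Conclusion.** The point holds as a sequencing weakness that should be fixed. It does not show that T0 is contaminated. The stated times do not protect T0 from knowledge of the arm: 0 to 10 of about 15 baseline minutes follow disclosure if log-in is at −10, and up to 15 if the intervention is counted from familiarisation. These ranges rest on the three assumed placements and on taking the stated times at face value.

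T0 saliva, pulse and oxygen saturation are exposed. T0 Venham scores may be, but no clock time is given for them. The comparisons at risk are the physiological changes from baseline, the before-and-after amylase comparison, and any use of T0 anxiety in the T2 comparison. The documents give no basis for putting a size or direction on the bias, so none is claimed. Recruitment and completion rates are unaffected, which keeps this below the level of a fault that undermines the pilot.

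**What to change.** - State that all T0 measures (Venham scores, pulse and oxygen saturation, saliva collection) are completed and entered before the allocation is opened.
- Enforce this in REDCap by making the T0 form mandatory before the randomisation step. Because the amylase result comes later from the laboratory, the form should record that the swab was taken, and when.
- Reconcile the two 10-minute marks by starting baseline earlier. If log-in stays at −10, baseline begins at about −25 and the swab precedes log-in. The late announcement, and its benefit against foreknowledge, is kept.

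The cost is a few minutes' earlier arrival and a form lock. Ethical Considerations has paper forms transferred to REDCap afterwards, so the T0 form would have to be entered at the visit.

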### Statistical Analysis

Analysis will be conducted using the SAS (SAS Institute) statistical analysis software (version 9.4). Descriptive statistics, by treatment, will be conducted for demographic and clinical variables and will be used to present sociodemographic and clinical data, parent and health care professional satisfaction levels, and procedural time. Due to a small sample size, we will also assess effect sizes.

For the pilot project, we plan to perform descriptive analyses of the sample as well as comparative analyses between the 2 groups. Nonparametric tests for procedural type, age, parental presence, parental and health care satisfaction levels, and baseline (T0) anxiety score measurement will be used to assess the composite outcome for mean salivary cortisol level and mean difference in anxiety score (using the Venham Clinical Cooperation Scale and Venham Clinical Anxiety Scale) between the experimental and control groups at T2. Analyses will be carried out according to the intention-to-treat principle, with a significance level (α) of .025, considering Bonferroni's correction.

For secondary outcome analyses, nonparametric tests adjusted for procedural type, age, and parental presence will be used to assess the mean procedural length at T2 using the VAS and 6-item tailored questionnaire, respectively. Comparison of dichotomous variables including the necessity for procedural retakes, use of other nonpharmacological interventions, and the occurrence of side effects will be assessed using the Cochran-Mantel-Haenszel test.

The study data will be recorded in the REDCap system belonging to URCA. The data manager associated with URCA and independent of the study will be responsible for the storage of the recorded data. However, a URCA biostatistician independent of the study will be responsible for the data analysis. The data analysis plan will be discussed with the principal investigator ([name]). Interjudge correlations will be conducted for the video tape analysis. Two judges will independently rate the anxiety measure on the videotapes. Subsequently, we will conduct intraclass correlation coefficient analyses to compare the scores for each of the recruited patients between the 2 judges.

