### Objectives

The primary research objectives are to determine (1) the feasibility and acceptability of VR distraction for children with special needs requiring dental procedures, (2) compare parent and health care professional satisfaction levels between the VR distraction group and the clinic’s standard mounted TV showing cartoons, and (3) observe the preliminary effects of VR distraction on reducing patient anxiety during dental procedures compared with standard nonpharmacological behavior management.

The secondary objectives of this study are to compare the following between the VR distraction group and the clinic’s standard mounted TV showing cartoons: (1) physiological parameters (pulse and oxygen saturation), (2) the occurrence of side effects, (3) dental procedure length, (4) the number of retakes of dental procedures due to DFA, and (5) salivary amylase levels.

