### Study Time Points

Sociodemographic data will be assessed before the intervention at baseline (T0) to establish a baseline using a simple questionnaire completed by the parent or legal guardian present while sitting in the waiting room. Salivary alpha-amylase samples will be collected at T0 and after the intervention/procedure (T2; Multimedia Appendix 1). Measures of specific dental procedure–related anxiety and uncooperative behavior will be assessed at T0, during the procedure (10 minutes from the start; T1), and immediately after the end of the procedure (T2). Physiological parameters will be measured at T0, during the intervention (T1), and T2. Data on occurrence of side effects will be assessed and monitored at all times for the duration of this study. All clinical monitoring will be performed by the dental resident on site. Measures of parent or legal guardian and health care professional satisfaction will be assessed at T2.

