#### Primary Outcomes

To measure feasibility and patient acceptability, we will record patient recruitment rates, completion rates of planned procedures, and satisfaction. As this is a population of children with SHCN, we estimate 50% of patients will agree to participate during recruitment, and we expect a completion rate of planned procedures of 75%.

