#### Measures of Primary Outcomes

Parent or legal guardian satisfaction with the intervention will be assessed using a visual analog scale (VAS; 0-10, where 0 is very dissatisfied and 10 is very satisfied) and the question recommended by the Pediatric Initiatives on Methods, Measurement and Pain Assessment in Clinical Trials (PedIMMPACT): “Considering anxiety relief, side effects and emotional recovery, how satisfied were you with the intervention used to manage DFA experienced by your child?” [22] (Multimedia Appendix 2). The parent or legal guardian will respond according to their satisfaction level.

Health care professional satisfaction with the intervention will be assessed using a VAS (ranked from 0-10, where 0 is very dissatisfied and 10 is very satisfied) as well as a 6-question satisfaction questionnaire (each answer will be given a score of 1, 2, 3, or 4 based on the choice of answer: Fortement en désaccord, En désaccord, En accord, Fortement en accord, respectively) and will result in a final score between 6 and 24 (Multimedia Appendix 3).

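### As most naturally read, the T2 anxiety and biomarker comparison is adjusted for parent and professional satisfaction, which are post-treatment outcomes and not baseline covariates

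*Protocol article*

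**What the plan says.** All references are to the protocol article.

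- **Statistical Analysis, main comparison.** The list reads: "Nonparametric tests for procedural type, age, parental presence, parental and health care satisfaction levels, and baseline (T0) anxiety score measurement will be used". The purpose given for these tests is "to assess the composite outcome for mean salivary cortisol level and mean difference in anxiety score", contrasting the two arms at T2. The paragraph then promises intention-to-treat analysis at α = .025.
- **Statistical Analysis, secondary outcomes.** The next paragraph says that "nonparametric tests adjusted for procedural type, age, and parental presence will be used". These are the first three variables of the main list. Satisfaction and the T0 score are not repeated.
- **Study Time Points.** "Measures of parent or legal guardian and health care professional satisfaction will be assessed at T2", that is, after the procedure.
- **Primary Outcomes.** For feasibility and acceptability, "we will record patient recruitment rates, completion rates of planned procedures, and satisfaction".
- **Objectives.** The second primary objective is to "compare parent and health care professional satisfaction levels between the VR distraction group and the clinic’s standard mounted TV showing cartoons".
- **Measures of Primary Outcomes.** The parent item reads: "Considering anxiety relief, side effects and emotional recovery, how satisfied were you with the intervention used to manage DFA experienced by your child". Professionals give a 0-10 rating of the intervention and answer six items, whose wording is in an appendix not shown here.
- **Study Proceedings.** Staff, children and parents cannot be blinded.

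**The concern.** A covariate in a randomised comparison should be something that treatment cannot have changed. Satisfaction fails this test in two ways. It depends on treatment directly, because unblinded respondents rate the intervention they saw. It also depends on the outcome: a parent asked to weigh anxiety relief will tend to score higher when the child was calmer.

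Comparing the arms among children with equal satisfaction therefore no longer estimates the effect of allocation on anxiety. Part of a true benefit is absorbed by the covariate. If VR raises satisfaction for reasons unrelated to anxiety, such as novelty, a VR child with the same satisfaction as a TV child will tend to be the more anxious of the two, and a difference appears where none exists. A larger sample would not cure this.

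At stake is the third primary objective, the preliminary effect of VR on anxiety. Recruitment and completion rates are untouched.

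**Working it through.** **1. The article's own figures.** 0.10 × 200 = 20 children and 0.05/2 = .025. Both reproduce, and neither is in dispute. The article gives no effect size, standard deviation or correlation for this comparison, so every value of d, r and g below is an assumption shown as a range.

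**2. Is the list an adjustment list?** Three features say yes. The stated target of the tests is the T2 composite, not the listed items. The list contains the T0 anxiety score, the usual covariate for a later anxiety score. The next paragraph attaches *adjusted for* to the same first three variables.

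**3. One satisfaction score, no T0 term.** Let anxiety be Y = −d·T + e with within-arm SD 1 (T = 1 for VR). Let satisfaction be S = −r·Y + g·T + u with var(u) = 1 − r². Here r is the strength of the within-arm correlation and g is any direct effect of allocation on satisfaction, in SD. The within-arm slope of Y on S is −r, and the arms differ in S by r·d + g. So:

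adjusted effect = −d + r(r·d + g) = −d(1 − r²) + r·g

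A simulation of 400,000 records agreed with this formula. With a true effect of −0.80:

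| r | g = 0 | g = 0.5 |
|---|---|---|
| 0.3 | −0.73 | −0.58 |
| 0.5 | −0.60 | −0.35 |
| 0.7 | −0.41 | −0.06 |

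With d = 0.5, r = 0.7 and g = 0.5 the sign reverses: −0.255 + 0.35 = +0.095. With d = 0 and g = 0.5 the spurious effect against VR is +0.15, +0.25 and +0.35 for r = 0.3, 0.5 and 0.7. If g were negative (for instance, if the headset annoyed professionals), the r·g term would flatter VR instead.

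**4. Two satisfaction scores, T0 adjusted.** Give T0 a coefficient of 0.5, which leaves a variance of 1 − 0.25 = 0.75. Let k = 2 if the two scores' errors are independent and k = 1 if they are fully shared. Then:

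retained share = (1/0.75) / [(1/0.75) + k·r²/(1 − r²)]

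At r = 0.5 and k = 2 this is 1.333/(1.333 + 0.667) = 0.67. Shrinkage across the models with g = 0:

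| r | one score, no T0 (r²) | shared errors, k = 1 | independent errors, k = 2 |
|---|---|---|---|
| 0.3 | 9% | 7% | 13% |
| 0.5 | 25% | 20% | 33% |
| 0.7 | 49% | 42% | 59% |

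With d = 0 and g = 1, the spurious effect is [k·r/(1 − r²)] divided by the same denominator: 0.23, 0.40 and 0.60 SD for k = 1, and 0.43, 0.67 and 0.84 SD for k = 2.

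**5. At N = 20, two-sided α = .025 (sidedness assumed).** Simulated rejection rates compare a Mann-Whitney test without satisfaction with a rank ANCOVA that includes one satisfaction score, on continuous data.

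- d = 0.8: about 0.23 without satisfaction. With it, 0.19 (r = 0.5) and 0.13 (r = 0.7) at g = 0; 0.055 and 0.019 at g = 0.5.
- d = 0: about 0.02 without satisfaction. With it, 0.026 and 0.027 at g = 0; 0.040 and 0.071 at g = 0.5; 0.058 and 0.163 at g = 1.

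**The case against.** The main sentence says tests *for* these variables and never says adjusted for them. In the abstract, nonparametric tests are mentioned alongside demographic and clinical variables and the presentation of satisfaction, which suggests that satisfaction was meant to be tested as an outcome. The secondary sentence is itself garbled: it assesses procedural length with the rating scale and six-item questionnaire, which are the satisfaction instruments. That again hints at satisfaction as an outcome. The main sentence also names cortisol, although the protocol measures alpha-amylase, so its wording cannot bear much weight.

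This stands in part. A reader might infer that the article states outright that it will condition on satisfaction; it does not, and the covariate reading is an inference, though the most natural one. The objection does not rescue the sentence, because an analyst following it could include satisfaction.

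Other stronger readings also go beyond the text:

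- **A biased effect size feeding the main trial.** The 200 is already given as expected and the 20 derived from it. Effect sizes are promised separately, without saying that they come from the adjusted test. The Conclusion says only that the results can serve as preliminary data.
- **Parental presence as a treatment effect.** The same one-parent rule applies in both arms, and nothing suggests that allocation changes it.
- **The professional items ask about anxiety relief.** That wording is documented only for the parent item. The professional rating is still post-treatment, unblinded and about the intervention, so the argument does not depend on it.

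**Conclusion.** The point holds in this form: as most naturally read, the plan adjusts the T2 anxiety and biomarker contrast for two variables that lie downstream of treatment and probably of the outcome. Attenuation follows if satisfaction falls as anxiety rises and allocation has no other influence on satisfaction; the wording of the parent item makes the first condition likely. A direct influence of allocation on satisfaction adds a spurious component, against VR if positive and in its favour if negative.

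The size is illustrative only. Shrinkage of about 7% to 59% rests on assumed r of 0.3 to 0.7, on how far the two scores share error, and on linear models, whereas the plan is nonparametric. No single figure in that range should be read as the expected bias.

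**What to change.** In the Statistical Analysis sentence, delete parental and health care professional satisfaction from the list of variables. State that both are analysed only as outcomes compared between arms, in line with the second primary objective. Replace *for* with *adjusted for*, and limit adjustment of the T2 anxiety comparison to pre-randomisation variables, chiefly the matching T0 Venham score.

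Keep the number small. The current list has six items for 20 children, and more terms if procedure type has several levels. Age and procedure type are legitimate candidates. Which further baseline factor to keep, if any, and which rank method to use can be left to the statistician.

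The cost is one or two sentences of analysis text, with no change to conduct, data collection or sample size.
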